#### Economic evaluation

The feasibility work will be used to test the performance of the data collection forms and methods. For the EQ-5D-5 L (and proxy EQ-5D-5 L) it is anticipated that performance will include assessment of clarity of concept (as evidenced by number of missing data (> 75% completed)). Integral to this part of the study is the acceptability of the EQ-5D-5 L (and proxy EQ-5D-5 L) to residents and their staff informants, evidenced by completion.

The feasibility of obtaining routinely collected health service use data from hospital records and GP administrative systems (e.g. SystmOne) in the timeframes required will be assessed. This will be compared against collection of data from care home notes (as described earlier) to assess the optimal methods of data collection for this population and in this setting.

Training details (number of sessions, number of attendees, number of trainers and duration of sessions) will be collected in order to provide a detailed breakdown of the cost of delivering the intervention.

### Sample size

The trial is designed to determine feasibility, not to evaluate effectiveness; therefore a formal power calculation is not appropriate. However, since we wish to assess whether change in our proposed primary outcome for a definitive trial, the PAM-RC, is feasible it is important that we have sufficient participants to make a preliminary and non-definitive randomised comparison of SCTP with UC. Our target sample size of 10 homes, each with 12–15 residents, allows us to detect a minimally important clinical difference of 0.5 standard deviation (SD) units with 80% power, a more relaxed false-positive error rate of 0.20 appropriate at this stage of the evaluation, 25% loss to follow-up and an ICC of 0.03 to 0.05.

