### Care home randomisation

Following confirmation of eligibility and consent (or consultee agreement), and subsequent to baseline assessments with/about participating residents, at the level of the home and from individual staff members, care homes will be randomised on a 1:1 basis to receive SCTP or UC. Randomisation will be performed by the statistical team at the Clinical Trials Research Unit (CTRU), using block randomisation with randomly selected block sizes. Concealment of sequencing is ensured by the physically separate locations of the CTRU and the blinded study researchers.

Following randomisation, the CTRU statistical team will inform the unblinded members of the research team of the randomisation outcome, so that arrangements for training in the intervention can be made for those homes allocated SCTP. Unblinded members of the research team will be informed of the random allocation of the last two homes at the same time, to avoid predictability of care home allocation and selection bias in the recruitment of homes and/or residents. An unblinded member of the research team will inform the care home manager of the treatment allocation by telephone and email. This same member of the team will arrange follow-up visits with managers in an effort to keep researchers undertaking outcome assessment blind to allocation throughout the trial. This will ensure researcher follow-up visits are not arranged at the same time as intervention training sessions within the home and will allow reinforcement of the need to not divulge allocation details.

To ensure sufficient outcome data for evaluation at six months, despite initial assessment that there should be 12–15 eligible residents at a participating care home, a minimum of eight participating residents will be accepted for homes to proceed to randomisation.

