### Analysis

#### Quantitative analysis

The analysis plan outlined here will be reviewed and a final, more detailed statistical analysis plan will be written before any analysis is undertaken. Any changes to the finalised analysis plan and reasons for change will be documented. Final analysis will be carried out when all available outcome data have been received. Analyses will focus on descriptive statistics and confidence interval (CI) estimation, with the exception of potential efficacy.

The recruitment strategy will be assessed by summarising the screening, eligibility, consent and randomisation stages at both the care home and resident level. Care home and staff demographics will be summarised to inform the context in which the trial was conducted.

Delivery of the SCTP will be evaluated by summarising staff attendance at the sessions, as well as feedback on engagement, content and delivery of the sessions. This will be assessed alongside the qualitative analysis from the process evaluation.

To assess feasibility and acceptability of follow-up, retention of homes and residents—including the number, timing and reasons for withdrawal—will be reported by trial arm to examine whether there are any systematic differences between the arms which could be attributed to the intervention. The difference in follow-up rates between the arms and corresponding CI will also be reported.

To inform the choice of primary and secondary outcomes for a definitive trial, completeness of outcome data will be summarised overall and by arm to assess both the acceptability of the measures and methods for collecting the data in a definitive trial. Point estimates and variability (SD) of the outcomes at each time point will be calculated by arm, together with 80% CIs for the difference in outcomes between the arms at six months using methods appropriate for cluster randomised trials with a small number of clusters [32]. The amount of missing data will also be presented.

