To obtain a preliminary and non-definitive randomised comparison of the SCTP with UC for the PAM-RC, hypothesis testing will be conducted at the 20% significance level using the t-test on care home (cluster) level summaries. Adjustment for covariates will be carried out using a two-stage process. At the first stage, a standard regression model including the covariates of interest, but excluding the intervention effect, will be fitted to calculate cluster-specific expected values. Expected and observed values will be compared by computing a residual for each cluster. These cluster level residuals will then be analysed using methods based on the t-test in the second stage of analysis [31].

To inform the sample size/power calculation for a definitive trial, the SD of the PAM-RC score in the intervention and control arms will be assessed to confirm the SD to be used. The minimum clinically important difference will be established via the mean scores (and 80% CIs) in the control arm and by seeking clinical opinion. An estimate of the clustering effect (ICC) and 95% CI as well as cluster-size variation (coefficient of variation) relating to the PAM-RC will also be provided.

AEs, pressure sores, number of resident falls, hospitalisations and deaths will be summarised by arm to assess the safety of conducting a trial in this setting. Staff physical health issues and sickness levels will also be summarised by arm to ensure that the intervention is not having a negative impact on staff wellbeing.

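### The stated 80% power for 0.5 SD matches a large-sample formula; the planned 8-df cluster-level t-test, read as two-sided, gives about 73–82% before covariate adjustment

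*Protocol article*

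**What the plan says.** The Sample size section first says that a formal power calculation is not appropriate for a feasibility trial. It then gives one to support a preliminary comparison on the PAM-RC. The inputs are "Our target sample size of 10 homes, each with 12–15 residents", "a more relaxed false-positive error rate of 0.20 appropriate at this stage of the evaluation", and "25% loss to follow-up and an ICC of 0.03 to 0.05". The claim is that this "allows us to detect a minimally important clinical difference of 0.5 standard deviation (SD) units with 80% power".

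The Quantitative analysis section fixes the test: "hypothesis testing will be conducted at the 20% significance level using the t-test on care home (cluster) level summaries". A two-stage covariate adjustment based on cluster residuals is also planned. Neither section says whether the test is one- or two-sided. The same section reports "80% CIs for the difference in outcomes between the arms at six months using methods appropriate for cluster randomised trials" with few clusters.

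Under Care home randomisation, "care homes will be randomised on a 1:1 basis to receive SCTP or UC", so five homes per arm are expected. That section also says that "a minimum of eight participating residents will be accepted for homes to proceed to randomisation". Trial status reports 124 residents in the nine homes randomised by 23 February 2018.

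**The concern.** The power statement and the planned test are both in the article, so they can be checked against each other. A t-test on ten home-level summaries has 10 − 2 = 8 degrees of freedom. Its two-sided 20% critical value is 1.397, against 1.282 for the normal distribution. A power figure that takes account of the ICC but not of the small number of homes will therefore be too high for this test.

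This is the article's only quantitative support for the PAM-RC comparison. If the figure is too favourable, a non-significant result would be read as somewhat stronger evidence against a 0.5 SD effect than the design can give.

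**Working it through.** **Inputs (protocol article).** Five homes per arm; 12 or 15 residents recruited per home; 25% loss, so m = 0.75 × 12 = 9 or 0.75 × 15 = 11.25 analysed per home; ICC 0.03 or 0.05; difference d = 0.5 SD; alpha 0.20. Assumptions: a two-sided test, equal home sizes and no covariate gain.

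**Step 1: effective sample size per arm.** n_eff = 5m / [1 + (m − 1) × ICC].

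- 12, ICC 0.03: 45 / 1.24 = 36.3
- 12, ICC 0.05: 45 / 1.40 = 32.1
- 15, ICC 0.03: 56.25 / 1.3075 = 43.0
- 15, ICC 0.05: 56.25 / 1.5125 = 37.2

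**Step 2: reproduce the stated 80%.** The normal formula requires 2 × (1.2816 + 0.8416)² / 0.5² = 36.06 per arm. The effective sizes 36.3 and 37.2 just meet this, 43.0 exceeds it and 32.1 misses it. The stated figure therefore reproduces if 12 residents are paired with ICC 0.03 and 15 with ICC 0.05.

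**Step 3: power of the planned test.** The noncentrality parameter is 0.5 × √(n_eff / 2). Power comes from the noncentral t distribution with 8 df and critical values ±1.397.

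| Residents per home | ICC | Noncentrality | Normal formula | t-test, 8 df | Difference detectable with 80% power (8 df) |
|---|---|---|---|---|---|
| 12 | 0.03 | 2.130 | 80.2% | 76.9% | 0.53 SD |
| 12 | 0.05 | 2.004 | 76.6% | 73.2% | 0.56 SD |
| 15 | 0.03 | 2.319 | 85.0% | 82.0% | 0.48 SD |
| 15 | 0.05 | 2.156 | 80.9% | 77.7% | 0.52 SD |

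Simulating the t-test on home means (400,000 runs per scenario) gives the same four values: 76.9%, 73.2%, 82.0% and 77.7%. To reach 80% on 8 df needs about 13.7 recruited per home at ICC 0.03, which is inside the target range, and about 17.0 at ICC 0.05, which is above it.

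**Step 4: recruitment to date.** 124 / 9 = 13.8 residents per home, or 10.33 analysed after 25% loss. With ten equal homes of this size, power is 80.1% (ICC 0.03) or 76.0% (ICC 0.05).

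**Step 5: lower bound.** If every home recruited just eight (m = 6), power would be 66.7% (ICC 0.03) or 64.2% (ICC 0.05).

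**Step 6: sidedness.** A one-sided 20% test on 8 df would give 87–92% over the target ranges.

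**The case against.** Five points can fairly be made for the article.

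- **The 80% is not a calculation slip.** It follows from a standard design-effect formula, and the two ranges may be meant to move together (12 with ICC 0.03, 15 with ICC 0.05). This stands in part. On that reading the 12/0.05 corner is not claimed, and the shortfall is only 2 to 3 points (77.7% and 76.9%). The planned test still misses 80% at both pairs, and the text does not say that the ranges are paired.
- **Sidedness is inferred.** This stands as a caveat. However, one-sided power of 87–92% does not match a stated 80%, the two-sided normal formula does, and 80% confidence intervals correspond to a two-sided 20% test.
- **Covariate adjustment may recover the loss.** This is possible. As an illustration, if covariates correlate with the outcome at 0.4 at both resident and home level (an assumption), the detectable effect scales by 1/√(1 − 0.16). Power at the four corners, in table order, becomes about 82%, 78.5%, 87% and 83%. The Sample size section claims no such gain, and unequal home sizes, also uncounted, would act the other way.
- **The trial is a feasibility study.** The comparison is labelled preliminary and non-definitive, and the progression areas named are recruitment, intervention delivery, data collection and follow-up, not the PAM-RC test. This limits the severity. It does not make the stated figure right for the stated test.
- **The eight-resident minimum says little about expected power.** This stands. A reader might infer from it that the trial has only 64–67% power. That would need all ten homes to sit at a minimum that applies home by home, whereas the reported mean is 13.8.

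**Conclusion.** The point holds as a modest overstatement. For 0.5 SD, the planned test has about 73–82% unadjusted power over the stated ranges, and it falls about 2 to 7 points below 80% at three of the four corners. At the least favourable corner the chance of missing a 0.5 SD effect is about 27% rather than 20%. At reported recruitment, power is on target if the ICC is 0.03 and about 4 points short if it is 0.05.

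These figures assume a two-sided test, five homes per arm, equal home sizes, 25% loss and no gain from covariates. The documents do not support reading this as a trial with too few homes for its purpose, or as one whose progression decision is compromised. Severity is minor to moderate.

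**What to change.** In the Sample size section, and in the statistical analysis plan if it repeats the figure:

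1. State that the 20% test is two-sided.
2. Replace the 80% claim with power of about 73–82% for 0.5 SD under the 8-df cluster-level t-test, before covariate adjustment and assuming equal home sizes. Equivalently, state 80% power for a difference of 0.48–0.56 SD.
3. If the eight-resident minimum is mentioned, give 64–67% only as the lower bound that would apply if every home recruited just eight.

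The cost is wording only. No extra homes or residents are needed and the analysis does not change; the stated power becomes slightly less favourable.

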### Analysis

#### Quantitative analysis

The analysis plan outlined here will be reviewed and a final, more detailed statistical analysis plan will be written before any analysis is undertaken. Any changes to the finalised analysis plan and reasons for change will be documented. Final analysis will be carried out when all available outcome data have been received. Analyses will focus on descriptive statistics and confidence interval (CI) estimation, with the exception of potential efficacy.

The recruitment strategy will be assessed by summarising the screening, eligibility, consent and randomisation stages at both the care home and resident level. Care home and staff demographics will be summarised to inform the context in which the trial was conducted.

Delivery of the SCTP will be evaluated by summarising staff attendance at the sessions, as well as feedback on engagement, content and delivery of the sessions. This will be assessed alongside the qualitative analysis from the process evaluation.

To assess feasibility and acceptability of follow-up, retention of homes and residents—including the number, timing and reasons for withdrawal—will be reported by trial arm to examine whether there are any systematic differences between the arms which could be attributed to the intervention. The difference in follow-up rates between the arms and corresponding CI will also be reported.

To inform the choice of primary and secondary outcomes for a definitive trial, completeness of outcome data will be summarised overall and by arm to assess both the acceptability of the measures and methods for collecting the data in a definitive trial. Point estimates and variability (SD) of the outcomes at each time point will be calculated by arm, together with 80% CIs for the difference in outcomes between the arms at six months using methods appropriate for cluster randomised trials with a small number of clusters [32]. The amount of missing data will also be presented.

To obtain a preliminary and non-definitive randomised comparison of the SCTP with UC for the PAM-RC, hypothesis testing will be conducted at the 20% significance level using the t-test on care home (cluster) level summaries. Adjustment for covariates will be carried out using a two-stage process. At the first stage, a standard regression model including the covariates of interest, but excluding the intervention effect, will be fitted to calculate cluster-specific expected values. Expected and observed values will be compared by computing a residual for each cluster. These cluster level residuals will then be analysed using methods based on the t-test in the second stage of analysis [31].

To inform the sample size/power calculation for a definitive trial, the SD of the PAM-RC score in the intervention and control arms will be assessed to confirm the SD to be used. The minimum clinically important difference will be established via the mean scores (and 80% CIs) in the control arm and by seeking clinical opinion. An estimate of the clustering effect (ICC) and 95% CI as well as cluster-size variation (coefficient of variation) relating to the PAM-RC will also be provided.

AEs, pressure sores, number of resident falls, hospitalisations and deaths will be summarised by arm to assess the safety of conducting a trial in this setting. Staff physical health issues and sickness levels will also be summarised by arm to ensure that the intervention is not having a negative impact on staff wellbeing.

#### Qualitative analysis

Transcribed interviews and fieldwork notes will be entered into NVivo computer software to facilitate management of a large dataset and the analytic process. A thematic framework approach [33] to data analysis will be employed to develop understanding of the facilitators and barriers to implementation of the SCTP in the care homes. Particular attention will be paid to staff’s views and experiences of the programme as well as the factors that facilitate or inhibit delivery or sustainability of the intervention over time. Findings will inform the development of the implementation process for a full-scale trial.

#### Economic analysis

While the primary aim of the economic analysis is to test the feasibility of data collection for any subsequent RCT, analysis of the data collected will include descriptive statistics of the resources used. Unit costs for health service resources will be obtained from national sources such as the PSSRU [34], the BNF [35] and NHS Reference cost database [36]. The perspective of the NHS will be adopted.

#### Progression criteria for continuation to a definitive randomised controlled trial

Guidelines for progression to a definitive RCT are based on a traffic light system of green (proceed to RCT design), amber (review RCT design and/or implementation, then proceed) and red (stop and do not proceed). Progression would be contingent upon meeting success criteria in the areas of participant recruitment, intervention delivery, data collection and follow-up. Progression criteria are detailed in Additional file 1.

### Trial organisation and governance

The PATCH trial is sponsored by the Bradford Teaching Hospitals NHS Foundation Trust and is coordinated by the Academic Unit of Elderly Care and Rehabilitation (Bradford Teaching Hospitals NHS Foundation Trust and University of Leeds) and the Clinical Trials Research Unit (CTRU) at the University of Leeds. The trial management group consists of the co-applicants and the teams from the coordinating units. The study will be conducted in accordance with the Research Governance Framework for Health and Social Care (2005) and CTRU standard operating procedures. The study protocol was written in line with the Standard Protocol Items: Recommendations for Interventional Trials (SPIRIT) 2013 Statement [37] and is reported in line with CONSORT 2010 statement’s extension to randomised pilot and feasibility trials [38, 39].

The SPIRIT checklist can be found in Additional file 2.

Overall trial supervision will be provided by the Trial Steering Committee (TSC) which will have an independent Chair. A sub-group of the TSC will perform a safety monitoring function since a separate Data Monitoring and Ethics Committee is not required for a feasibility trial of this nature and duration.

A patient and public involvement (PPI) group will be separately convened through existing networks at the Academic Unit of Elderly Care and Rehabilitation. They will be consulted at key time points during the trial to provide input to the content of participant materials, the acceptability of measures, any problems encountered with recruitment, interpretation of findings and dissemination of results.

Data will be entered, managed and monitored for quality and completeness by the CTRU. Missing data (except individual items collected via questionnaires) will be chased until received, confirmed as not available or the trial is at analysis. Data will be stored and managed in accordance with the provisions of the Data Protection Act (1998).

### Dissemination

Results of the study will be published in peer-review publications and will be presented at national and international conferences. We will work with the PPI group to develop lay reports to disseminate research findings to resident and relative groups and the care home staff at participating homes.

Authorship will be agreed in accordance with the PATCH trial publication policy and in line with International Committee of Medical Journal Editors recommendations.

## Discussion

The project team have built on their research experience in care homes [40, 41] to optimise implementation of this feasibility trial. This includes care home identification using the CQC database and personal engagement with a network of homes who have previously participated in research. Data collection methods focus on provision of data from multiple sources (residents, staff and routine data) to facilitate involvement of a generalisable sample of residents, i.e. those with and without capacity to consent who may or may not be able to provide information about themselves.

While this feasibility trial aims to refine recruitment of, and data collection from, care home residents and staff, a key focus relates to intervention delivery, receipt and enactment. This is a novel intervention which has not had widespread use; thus monitoring of implementation and exploration of barriers and facilitators that may hinder delivery and impact resident and staff experiences is critical. This will allow the team to further develop implementation procedures to optimise uptake in a definitive trial. Outcomes from the feasibility trial will inform processes for delivery of the definitive trial, as well as adding to the body of evidence for good practice in care home research.

### Trial status

The study is currently working to protocol version 5.0, dated 10 November 2017. Recruitment of care homes commenced in February 2017 and recruitment of residents in May 2017. As of 23 February 2018, nine care homes have been randomised with 124 residents recruited at these homes. The study has completed site selection and is projected to complete recruitment and randomisation by the end of February 2018.

## Abbreviations

6CIT: Six-item Cognitive Impairment Test
ADL: Activities of Daily Living
CCAM: Continuing Care Ability Measure
CI: Confidence Interval
CQC: Care Quality Commission
CSP: Chartered Society of Physiotherapy
CTRU: Clinical Trials Research Unit
EQ-5D-5 L: EuroQol 5-Dimension 5-Level
FAC: Functional Ambulatory Classification
GP: General Practitioner
ICC: Intra-class Correlation Coefficient
MCA: Mental Capacity Act
NHS: National Health Service
PAM-RC: Physical Activity and Mobility in Residential Care scale
PATCH: Posture and mobility training in care homes
P-CAT: Person-Centred Care Assessment Tool
PPI: Patient and public involvement
RCT: Randomised controlled trial
REC: Research Ethics Committee
SCTP: Skilful Care Training Package
SD: Standard deviation
SPIRIT: Standard Protocol Items: Recommendations for Interventional Trials
TSC: Trial Steering Committee
UC: Usual care
UK: United Kingdom
